### Methods in analysis to handle protocol non-adherence and any statistical methods to handle missing data {20c}

Multiple imputation (MI) will be used to adjust model estimates that include incomplete data. Specifically, we will generate multiple imputed datasets with missing values filled in using chained equations (MICE). Baseline characteristics will be imputed using predictive mean matching and missing outcomes will be imputed using joint linear mixed models. Regression models will be fitted to each imputed dataset and the results will be pooled to produce the final estimates for inference.

### Plans to give access to the full protocol, participant-level data, and statistical code {31c}

We will upload the final protocol to clinicaltrials.gov once all data has been collected. Deidentified data and statistical code will be made available to qualified investigators upon request.

## Oversight and monitoring

### Composition of the coordinating center and trial steering committee {5d}

The PI (SC) will oversee the research team and ensure all aspects of the protocol are followed. The PI will also run monthly meetings with all co-investigators (FP, TP, CZ, JM, MAB) to provide additional oversight regarding any issues that arise. A Data Safety Monitoring Board (DSMB) has also been developed consisting of a pediatrician specialized in Adolescent Medicine, a rehabilitation medicine scientist with expertise in concussion clinical care and research, and a senior research scientist with expertise in behavior change research regarding physical activity.

### Composition of the data monitoring committee, its role and reporting structure {21a}

The PI (SC) will oversee data monitoring to assess issues with missingness and ensure quality. All analysis will be completed by the study statistician (CZ). A DSMB has also been developed as described above.

### Adverse event reporting and harms {22}

Adverse events will be reported as per IRB and NIH guidelines. We will also utilize a data safety monitoring board (DSMB) who will address any safety or ethical concerns. Prior to the start of protocol use, the DSMB reviewed the study procedures and plans for safety monitoring. Over the course of the trial, the board will review the data collection procedures at multiple time points (approximately twice per year, depending on recruitment and issues that arise) and will monitor the occurrence of any adverse events. All potentially adverse events will be reported to the DSMB within 48 h of occurrence. These adverse events include deaths, suicide attempts, severe side effects from physical activity, study dropout, hospitalizations, and/or clinical deterioration defined as the development of new suicidal or homicidal behaviors.

Each year, the DSMB will receive a report that summarizes all serious and unexpected adverse events and the DSMB will produce a report that reviews and summarizes [1] the committee’s opinion as to the safety, confidentiality, and privacy of the study and if study investigators are adequately assuring safety, confidentiality, and privacy [2]; a progress summary towards recruitment and follow-up goals [3]; any concerns relating to serious or unexpected adverse events. This yearly summary will be forwarded to the principal investigators, who will submit it to the Seattle Children’s Research Institute IRB.

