#### Active control (stretching)

We chose to utilize an active control to (1) provide a measure of blinding (participants will be told they will receive one of two exercise interventions) and (2) improve retention in the control group. Control subjects will be provided a series of stretching exercises, which will also advance throughout the 6 weeks. Subjects will initially be given two stretches, primarily focused on the neck and upper back (e.g., cervical retraction, scapular retraction). Additional stretches will be added through weekly discussions with the health coach if subjects are successfully tolerating and completing initial stretches, adding approximately one new stretching exercise per week. Control subjects will also continue to receive usual care from their concussion providers. We have also successfully piloted this approach previously [16].

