### Strategies to improve adherence to interventions {11c}

#### Frequent contact with study staff via video conferencing

Youth in both groups will be contacted by the research staff weekly via HIPAA-compliant video conferencing to discuss barriers and facilitators to completing exercises, and assess frequency and severity of symptoms. The use of video conferencing was successful as a means of enhancing participant engagement in our prior studies in which we retained > 90% of intervention and control participants to 12-month follow-up [56].

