## Assignment of interventions: Blinding

### Who will be blinded {17a}

We will describe the study as a comparison between exercise programs, in order to blind participants as to whether they are in the intervention or control arm. The statistician will be blinded to intervention status by labeling the intervention variable non-specifically in the dataset (i.e., 1 and 2). The PI and research coordinators will not be blinded.

Procedure for unblinding if needed {17b}

Not applicable as this is not a pharmaceutical trial.

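### Severe symptoms and injuries are listed as adverse events only when attributed to physical activity, which risks their being recorded more readily in MSTEP than in the stretching control

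*Protocol article*

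**What the plan says.** Adverse event reporting and harms {22} gives the list: "These adverse events include deaths, suicide attempts, severe side effects from physical activity, study dropout, hospitalizations". It ends with "clinical deterioration defined as the development of new suicidal or homicidal behaviors". The list serves as a reporting trigger: "All potentially adverse events will be reported to the DSMB within 48 h of occurrence". A yearly summary is also planned: "Each year, the DSMB will receive a report that summarizes all serious and unexpected adverse events". The section refers to IRB and NIH guidelines for reporting as well.

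Under Intervention description {11a}, MSTEP is aerobic exercise that is stepped up over 6 weeks. The comparator, under Active control (stretching), is described thus: "Control subjects will be provided a series of stretching exercises, which will also advance throughout the 6 weeks". Those stretches start with two, mainly for the neck and upper back.

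On blinding, Who will be blinded {17a} says of participants: "We will describe the study as a comparison between exercise programs, in order to blind participants". Of staff it says: "The PI and research coordinators will not be blinded".

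The only retention figure comes from the team's prior studies, which "retained > 90% of intervention and control participants to 12-month follow-up".

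**The concern.** An adverse-event definition should let the same clinical event count in the same way in both arms. Here one item has a cause built into it, and that cause is the content of the experimental treatment. Deaths, suicide attempts, hospitalizations and new suicidal or homicidal behaviors need no such judgement. A severe headache, a severe spell of dizziness or an exercise injury that stays out of hospital does, because no other item on the list covers it.

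At stake is the safety information on symptomatic adolescents that the DSMB sees during the trial, and any later report of harms by arm. If a severe event in a control participant is not recorded because nobody links it to stretching, no later analysis can recover it.

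Study dropout raises a lesser issue. It is a retention outcome, not a harm in itself, yet it stands in the same list as deaths and hospitalizations. If the two kinds of event were ever added together, dropout could swamp the clinical events.

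**Working it through.** The article states no harms rate, harms comparison or adverse-event total, so there is no figure to reproduce. The check reads the list item by item and then uses labelled assumptions to show how size would depend on them.

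**1. Which items need a judgement of cause?**

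| Listed item | Cause needed before it counts? |
|---|---|
| Death | No |
| Suicide attempt | No |
| Severe side effect from physical activity | Yes |
| Study dropout | No, but not a clinical harm |
| Hospitalization | No |
| Clinical deterioration | No, but limited to suicidal or homicidal behaviors |

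A severe flare or injury without hospitalization can enter only through the third row.

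**2. How attribution affects recorded counts.** Let r be the true rate of such events, equal in both arms, n the number per arm, and a the probability that an event is attributed to physical activity. Recorded count = n × r × a. With 200 participants allocated 1:1, n = 100. Assume r = 4% and a = 0.9 in MSTEP; neither value is in the documents.

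| Assumed a in control | Recorded, MSTEP | Recorded, control | Ratio |
|---|---|---|---|
| 0.9 | 100 × 0.04 × 0.9 = 3.6 | 3.6 | 1.0 |
| 0.6 | 3.6 | 2.4 | 1.5 |
| 0.3 | 3.6 | 1.2 | 3.0 |

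The rate r cancels, so the ratio is a(MSTEP) / a(control) and only restates the assumption. If attribution is the same in both arms, the distortion disappears.

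**3. Dropout, if pooled with clinical events.** Prior retention above 90% implies dropout below 10%, so fewer than 20 of 200 if this trial does as well. Assume dropout d of 2%, 5% or 10% (4, 10 or 20 participants) and other listed events h of 1%, 2% or 5% (2, 4 or 10), in different participants. Dropout's share is d / (d + h):

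| | h = 1% | h = 2% | h = 5% |
|---|---|---|---|
| d = 2% | 67% | 50% | 29% |
| d = 5% | 83% | 71% | 50% |
| d = 10% | 91% | 83% | 67% |

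Unequal dropout would also create a difference. With 2% true harm in each arm, dropout of 5% versus 10% gives pooled rates of 7% versus 12% (ratio 12/7 = 1.7). Dropout of 5% versus 15% gives 7% versus 17% (ratio 17/7 = 2.4). With equal dropout there is dilution but no false difference. None of this arises if dropout is tabulated separately.

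**The case against.** The strongest case against is that the list is a reporting trigger, not an endpoint.

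- **No comparison is planned.** The statistical sections cover efficacy and mediation only. No between-arm harms test and no pooled adverse-event count is stated. This stands, and it rules out saying that a planned comparison is biased.
- **The list is open.** It is introduced by a word meaning that other events may qualify, and the section speaks of all potentially adverse events and of IRB and NIH guidelines. A reader might infer that a severe headache counts only if attributed to activity, but the text does not say so. Still, it names that kind of event in no other way, and the named items are what staff will look for.
- **No assessor of cause is named.** A reader might infer that unblinded staff make the judgement. The article says only that the investigator and coordinators are unblinded. Participants, a likely source of reports, are told that both programs are exercise, and a control event could also be attributed to activity. This reduces the risk without removing it.
- **Symptoms are collected in both arms.** The Health and Behavior Inventory (HBI) is completed weekly for 6 weeks and again at 3 and 6 months, and weekly calls in both groups ask about symptoms. This is a real safeguard against missing symptom worsening. But the HBI is a symptom score, not an event record, and as described it does not cover injuries.
- **Dropout reporting is defensible.** In a fully remote trial, dropout may be the first sign of harm. The DSMB's yearly report also treats follow-up progress separately from serious or unexpected events, so the inference that dropout masks safety signals in a mixed total has no support. Prior retention was similarly high in both arms. What remains is a point about tabulation.
- **The article is condensed.** A relatedness field or tables by coded arm may exist in the full protocol or the DSMB's plan. That could already supply part of the fix, but the stated wording of the item would still need changing.

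**Conclusion.** The point holds as a risk. The wording makes a causal judgement part of the only listed item that covers a severe, non-hospitalized symptom flare or injury, and the suspected cause is what distinguishes MSTEP from control. With the investigator and coordinators unblinded, such events may be recorded more readily in MSTEP.

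The documents do not support the stronger readings: that harms data will be biased, that unblinded staff are the designated judges, or that dropout will dominate what the DSMB sees. The size cannot be derived. The ratios of 1.0 to 3.0 and the dropout shares of 29% to 91% rest on assumed rates, and the shares matter only if dropout is pooled with clinical events, which nothing in the article proposes.

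The change is worth making because it is cheap and because events never recorded cannot be restored at analysis.

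**What to change.** In Adverse event reporting and harms {22}:

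1. Replace the item on severe side effects of physical activity with an arm-neutral one: any severe new or worsened symptom or injury, in either arm, whatever its suspected cause.
2. Record suspected relatedness to the study program in a separate field, so that it describes an event but does not decide whether it is recorded.
3. Keep reporting study dropout to the DSMB, but tabulate it by coded arm with the reason, apart from clinical adverse events, so that the two are never pooled.

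The cost is a wording change, one extra form field and slightly more recorded events, mainly in control. The sample size and primary analysis do not change.

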### Frequency and plans for auditing trial conduct {23}

The PI will lead study meetings each week with the research staff and will monitor for any concerns. The DSMB will meet approximately biannually, or as needs dictate.

### Plans for communicating important protocol amendments to relevant parties (e.g., trial participants, ethical committees) {25}

Changes in protocol will be communicated to the public via clinicaltrials.gov. If participants are actively engaged in the study, they will be notified of any changes that would affect their participation.

### Dissemination plans {31a}

Results from the proposed project will be disseminated widely through traditional pathways, first through conference presentations targeting academicians, primary care providers, and concussion specialists, and then via peer-reviewed publications in academic journals. Dissemination to community stakeholders will occur through local and national presentations. We will also work with Seattle Children’s Research Institute media channels to promote publications and presentations that arise from this work.

## Discussion

The MSTEP study is the largest study to date to evaluate the impact of subthreshold exercise on youth with concussion, and the only one to deliver an exercise intervention completely virtually. This study builds on several years of work [15–17], including exploration into the feasibility and acceptability of this approach, and pilot data regarding potential benefit for youth with concussion. Our team began by studying subthreshold exercise as it is delivered clinically at our institution [15], then worked to translate this intervention into a research space [16], and finally adapted our methodology such that the intervention could be delivered completely virtually [17]. We are now testing this approach in a randomized controlled trial with a large sample size, and will be able to examine not only intervention effects, but variation between subjects and across demographic factors.

The MSTEP study is also unique in that it has been powered to examine potential mechanisms underlying treatment effects, particularly whether increases in MVPA are responsible for benefit [9] or whether other processes may matter more, such as decreases in fear of concussive symptoms [16]. Exploring mediators of treatment effects is key to optimizing these approaches in the future, as this information can guide our decisions regarding how to amplify treatments in future work.

Prior studies of subthreshold exercise interventions required intensive in-person visits weekly over several months [8, 9, 11]. Removing the need for in-person visits and converting the intervention to a virtual space improves access to youth who are distant from a medical center and is thus essential for ensuring equitable access to treatment. Developing a virtual intervention also ensures that exercise interventions can be available to treat youth with concussion during times when in-person visits present greater risk, such as during a pandemic. We are excited to test this approach with a broader sample of youth to determine whether treatment effects remain robust as we scale up these methods.

## Conclusions

Subthreshold exercise interventions have been shown to be effective for youth with concussion [9, 10], but the approaches utilized require extensive in-person visits which impedes access for many youth, particularly those distant from a major medical center or those concerned about undertaking an in-person visit due to risk of infection. We are testing the efficacy of a virtually delivered subthreshold exercise program for youth with concussion (MSTEP), using HIPAA-compliant video conferencing and physical activity tracking. Findings from the MSTEP study will be of great interest to clinicians caring for youth with concussion and may lead to changes in guidelines of care.

Trial status

Date recruitment began: 3/22/21

Estimated date of recruitment end: 4/15/25

Protocol version 8

## Abbreviations

MSTEP: Mobile Subthreshold Exercise Program
PPCS: Persistent postconcussive symptoms
RCTs: Randomized controlled trials
BDNF: Brain-derived neurotrophic factor
PA: Physical activity
MVPA: Moderate-vigorous physical activity
REDCap: Research Electronic Data Capture
HIPAA: Health Insurance Portability and Accountability Act
NHANES: National Health and Nutrition Examination Survey
HRQoL: Health-related quality of life
HR: Heart rate
BPM: Beats per minute
HBI: Health and Behavior Inventory
LPA: Light physical activity
CDEs: Common Data Elements
SCAT5: Sport Concussion Assessment Tool, version 5
PedsQL: Pediatric Quality of Life Inventory
GAD7: Generalized Anxiety Disorder-7 item
PHQ9: Patient Health Questionnaire-9 item
ARCS: Adult Responses to Children’s Symptoms
ASWS10: Adolescent Sleep Wake Scale-10 item
FOPQ: Fear of Pain Questionnaire
ANOVA: Analysis of variance
SED: Sedentary behavior
BMI: Body mass index
LGCM: Latent growth curve modeling
MI: Multiple imputation
DSMB: Data Safety Monitoring Board
